|                                        | 
calculated by dividing the N of RAGT sessions (16x) performed by the patients, divided by the N of the scheduled RAGT training sessions over the 4 week study period, times 100 (Osterberg & Blaschke, 2005). The eligibility, recruitment and adherence rates will be calculated with their 95% CI according to the Wilson 'score' method cited by Newcombe (Newcombe, 1998); when the proportion is close to 0 or 1, a Poisson approximation as described by Brown and colleagues will be used (Brown et al., 2001). Furthermore, the number of (serious) adverse events and side effects will be reported. The first phase of the analysis will involve a descriptive analysis for all disease groups using the mean (SD) or median (range, 25th and 75th percentiles). The second phase of the analysis will include inferential statistics using a pre-post analysis of the data from the total sample (one group). For continuous data, a paired t-test will be performed and for ordinal data, a Wilcoxon Signed Rank test.
 |
| Timeline of the clinical investigation | 
Study-specific:
 
Recruitment duration: 15 months
 1.2.2022 Planned start: First Patient First Visit (FPFV)
 31.3.2023, 2022 Last Patient First Visit (LPFV)/Last Subject In (LSI)
 30.4.2023 Planned end: Last Patient Last Visit (LPLV)/Last Subject Out (LSO)
 
Patient-specific:
 
Active intervention duration: 4 weeks (baseline assessment, 4-week intervention, post-intervention assessment)
                                                                                                                                                                                                                                                                                                                                                                                                                                                                                                                                                                                         |
| Funding                                | 
This clinical investigation is a researcher driven study, which is conducted with the financial support of Tyromotion GmbH, Graz, Austria with respect to the and provision of a LEXO® for the study site. A Research Agreement has been signed between the Reha Zentrum Münster Betriebs GmbH (RZM) and Tyromotion GmbH.
 
The agreement states that the purpose of this Collaboration is to systematically collect, analyse, and publish protocols and data on the clinical use of the LEXO® robotic gait trainer in the inpatient setting. A prospective comparative multiple case study will be used to investigate a variety of patients with different main diagnosis.
                                                                                                                                                                                                                                                                                                                                                      |

|                      |                                                                                                                                                                                                                                                                                                                                                                                                                                                                                                                                                                                                                                                                                                                                                                                                                                     |
|----------------------|-------------------------------------------------------------------------------------------------------------------------------------------------------------------------------------------------------------------------------------------------------------------------------------------------------------------------------------------------------------------------------------------------------------------------------------------------------------------------------------------------------------------------------------------------------------------------------------------------------------------------------------------------------------------------------------------------------------------------------------------------------------------------------------------------------------------------------------|
|                      | 
TYROMOTION primarily aims to collect data on effectiveness (performance) and safety (adverse events, side-effects, and drop-outs) on the LEXO® robotic gait trainer, but also on usability and feasibility, and the quality of the product.
 
A Purchase Order has been signed between the two parties, where Tyromotion will provide a LEXO® robotic gait trainer for the Reha Zentrum Münster that will conduct the planned clinical investigation followed by a larger randomised controlled trial.
 
The people involved in decision-making about this funding have no influence on the planning, conduct and publication of the clinical investigation. None of the investigators or other members of the study team receive a financial compensation for their contributions in this clinical investigation.
 |
| Compliance Statement | 
This clinical investigation will be conducted in compliance with the clinical investigation plan, the current version of the declaration of Helsinki, the EN ISO 14155 as well as all national and local legal and regulatory requirements.
                                                                                                                                                                                                                                                                                                                                                                                                                                                                                                                                                                                  |

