|                      | 
investigation. If they express their interest in participating, they will be screened by a psychologist for cognitive impairment and for walking impairment using the Functional Ambulation Categories in addition to a neurological exam. If patients pass the screening (if Mini Mental State Examination <math>\geq 24/30</math> points, walking impairment, FAC 0-4/5 points)), written informed consent will be obtained from them, followed by a Baseline examination. Then, the clinical investigation intervention will be conducted for 4 weeks, and a semi-structured observation of the intervention at weeks 1 and 4. After the post-intervention examination, the clinical investigation will be terminated.
                                                                                                                                                                                                                                                                                                                                                                                                                                                                                                                                                                                                                                                                                                                                                                                                                                                                                                                                                                                                               |

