**Adverse events**

Any adverse events and side effects will be systematically recorded and evaluated using a formal log including the type of adverse event, dates, severity, causality differentiated into serious/non-serious, actions to restore or improve the patient's wellbeing and outcome of the event. Study related adverse events such as training-related injuries will be treated and paid for. Severe adverse events will lead to early clinical investigation termination. ***This monitoring will be performed throughout the study.***

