### ***Limitations***

- Low number of patients per diagnosis – due to low power, efficacy testing cannot be performed for the different disease groups but overall.
- Limited generalizability of results
- No control group
- No follow-up assessment

As outlined in Chapter 2.1, the purpose of this clinical investigation is to investigate the feasibility and acceptability and compare the preliminary effects of RAGT a mixed population with neurological diseases consisting of patients with stroke in the subacute and chronic phases and with severe and mild to moderate disability, MS, Parkinson's Disease, spastic para-or tetraplegia, mild to medium grade hereditary ataxia, acute or chronic inflammatory demyelinating polyneuropathy and motoneuron disease. A further purpose of this clinical investigation is to synthesise quantitative and qualitative results for examining causality i.e., the extent to which the RAGT intervention may have caused the outcomes.

The results from this study can be used for designing a full-scale randomised controlled trial. The study population and all study procedures have been specified a priori, the study team will strive to carry out all measures as planned and use a structured data documentation, management and evaluation as outlined in this clinical investigation protocol. The intervention of this study uses a standard RAGT protocol but is individualised and hence adapted to the different patient groups (Cases 1-8) and the individual performance level of the participants. Continuous monitoring for adverse events using a structured log and predefined evaluation criteria will be performed. Therefore, it is not expected that the limitations of this study negatively impact on the conduct of the clinical investigation, data quality and results.

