### 9.4 Serious incident - definition

A serious incident is any adverse event or any adverse reaction, which either

- Leads to death, or
- Is life-threatening, or
- Leads to lasting or serious disability or invalidity, or
- Makes inpatient treatment or an extension to inpatient treatment necessary (except for if the inpatient treatment was planned before participation in the study).

A distinction is made between a serious adverse event (SAE) or a serious adverse reaction (SAR), depending on whether it has a causal relationship with the study intervention.

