#### Documentation of adverse incidents (AE/AR)

During the intervention phase (Week 1 – Week 4), the occurrence of the aforementioned events will be recorded by the responsible employee at the study site and assessed by a member of the medical team (investigator, PI).

All incidents and findings must be documented in the patient files and then in the AE log in the CRF.

The following information is necessary:

- Type of adverse event (signs, symptoms or disease)
- Start and end of occurrence
- Severity
- Causality of the intervention
- Differentiation (serious/non-serious)
- Measures concerning the intervention or actions to restore or improve the patient's wellbeing
- Outcome of the event.

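### Nothing provides for following adverse events still open at the post-intervention examination (T2), and sections 4.8 and 9.7 give different recording windows

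*Protocol*

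**What the plan says.** **End of participation.** The synopsis (Study procedures) closes the patient's pathway at T2: "After the post-intervention examination, the clinical investigation will be terminated". Section 7.8 sets the end of the whole investigation at the last patient's last visit and treats that as the last data capture. The limitations in section 8.2 include "No follow-up assessment". Section 7.7 describes continued usual care after exit and mentions no safety data collection.

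**Recording window.** Section 9.7: "During the intervention phase (Week 1 – Week 4), the occurrence of the aforementioned events will be recorded". Section 4.8, on the adverse event log: "This monitoring will be performed throughout the study".

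**What must be recorded.** The log fields in section 9.7 include "Start and end of occurrence" and "Outcome of the event".

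**What makes an event serious.** One criterion in section 9.4 is "Leads to lasting or serious disability or invalidity". Another is that the event makes inpatient treatment, or a longer stay, necessary.

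**What counts as an event.** Section 9.2 includes events related to study procedures as well as to the intervention.

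**The concern.** Two required log fields and two seriousness criteria depend on how an event develops over time. An event that begins late in training, or at the T2 tests themselves, has little or no observation time left. Its end may come after T2. Disability may prove lasting, or a longer stay may be decided, only after T2. The protocol stops collecting data on the patient at that point and does not say who looks further.

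Adverse events are one component of the primary feasibility endpoint (section 4.8). A summary of device safety goes to the sponsor (section 7.8), and section 8.2 (planned statistical analysis) reports the number of serious events. With 28 patients that number is likely to be small, so one late upgrade that goes unrecorded could change the picture. Because this is a limit on what is collected, the analysis cannot repair it afterwards.

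The two recording windows raise a separate problem. Section 1.3 expects rare falls during the walking tests, and those tests are done at baseline and T2. Whether a fall there enters the log depends on which section the site follows.

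**Working it through.** **The plan's own figures.** The protocol states no event rate, event duration or safety follow-up window, so there is no figure on this point to reproduce. The frame does reproduce: 4 strata × 5 + 4 strata × 2 = 28 patients, and 4 sessions × 4 weeks = 16 sessions.

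**Is there room after T2 in the timeline?** Inputs are from section 5.6 and Table 8.
- The last patient's first visit is 31.3.2023 and the last patient's last visit is 30.4.2023, which is 30 days.
- Training starts on day 1 or 2 after inclusion, so four weeks end on day 28 or 29, that is 28 or 29.4.2023.
- T2 fits, with 1 to 2 days to spare. The last patient has no safety follow-up period.
- Section 4.5 can be read as placing T2 four weeks after training is completed. That would be 26 or 27.5.2023, after the stated last visit. The dates therefore support T2 directly after training, as in Table 8.

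**Is there another route for later data?**
- Section 10.6 names three entry points to the case report form: screening, baseline and post-intervention. That passage concerns questionnaires and performance tests, so it does not by itself bound the event log, but it foresees no later entry.
- Section 7.5 gives early leavers one final examination, also with a safety purpose. It doubles as the post-intervention test and leaves the same gap for an event still open on that day.
- Section 9.7 assesses all events together at the end of the study. No step brings information from after T2 into that assessment.

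**Do the two windows agree?** Section 9.7 gives Week 1 to Week 4; section 4.8 gives the whole study. Read literally, the first leaves out the baseline and T2 examinations. Section 5.2 describes the intervention phase as lasting from baseline testing until post-intervention testing. That moves the limits closer to the two examinations but does not clearly include T2. Even under section 4.8, a patient's window ends with participation.

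**How many events could be open at T2?** This is illustrative only; onset pattern and duration are assumptions.
- Uniform onset over 4 weeks, fixed duration of *d* weeks: share open = *d*/4. For *d* = 1, 1/4 = 25%. For *d* = 2, 2/4 = 50%.
- Uniform onset over 28 days, exponential duration with mean *m* days: share open = (*m*/28) × (1 − exp(−28/*m*)).

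| Mean duration (days) | Share open at T2 |
|---|---|
| 3 | 10.7% |
| 7 | 24.5% |
| 14 | 43.2% |
| 28 | 63.2% |

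The shares would be higher if events clustered in later sessions, when section 7.2 has difficulty progressed. They describe events without an end date at T2. They do not estimate how many would later be reclassified.

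**The case against.** A reader might go further and infer any of four things that the protocol does not support.

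- *The seriousness criteria cannot be applied to open events.* Section 9.4 says lasting **or** serious disability, and the second limb can be judged at T2. Whether an event makes a longer stay necessary can be judged prospectively, and section 9.7 gives the classification to a doctor.
- *The 24-hour report would not be triggered.* Section 9.8 starts the clock when someone becomes aware of a serious event that occurred during the study, with no cut-off at T2. An event from training that is recognised later as serious fits that wording.
- *Open events will be filed as non-serious with outcome unknown.* No section says so. The log form and the assessment scheme (Figure 6) are not visible in the text reviewed, so a code for ongoing events may exist.
- *Adverse events are undercounted.* An open event that began in the window is still counted.

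There are further points on the other side. The listed limitation about follow-up most naturally concerns outcome testing. Section 1.3 expects mainly reversible fatigue and mild muscle pain, which seldom become lasting disability. Section 12.4 obliges patients to report health damage to the investigator, patient records are source documents (section 10.4), and joint assessment at the end of the study comes well after T2 for most patients.

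These points narrow the finding to end date, final outcome and late upgrade. They do not remove it. The reporting duty depends on awareness, and nothing makes anyone look at the chart after T2. Section 12.4 is an insurance condition, not a data collection step. The conflict between sections 4.8 and 9.7 also remains.

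**Conclusion.** The point holds in limited form. For an event open at T2, the end date, the final outcome and any change to serious that shows itself only afterwards are not assured of capture, although section 9.7 requires the first two. Sections 4.8 and 9.7 give different recording windows. On a literal reading of section 9.7, events at the baseline and T2 tests fall outside the window even though section 9.2 counts them.

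The size cannot be determined from the protocol. Under the stated assumptions, the share of events open at T2 ranges from about 11% (mean duration 3 days) to 63% (mean duration 28 days). The share misclassified would be smaller and is unknown. The conclusion rests on T2 falling directly after training, which the dates support, and on there being no follow-up rule in documents not shown here. An amendment is worthwhile because the gap lies in data collection for a primary endpoint component and is cheap to close.

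**What to change.** 1. Reconcile sections 4.8 and 9.7 to one recording window, from inclusion through T2, with both examinations included.
2. Add to section 9.7 that any event open at T2, or at an early-exit examination, is followed in the patient chart, within the limits of the patient's consent, until it is resolved or stable or the patient is discharged from the centre. Outcome and seriousness under section 9.4 are updated at that point. An event still open then is coded 'ongoing at last contact'.
3. State that an upgrade to serious at that stage falls under section 9.8.
4. Clarify in the synopsis that T2 ends outcome testing and that the chart check for open events may come later.

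**Cost.** A few sentences in the protocol and a chart check at discharge for patients with an open event, with no extra visit. Database closure may have to wait for the last discharge. Follow-up to discharge will still miss disability that proves lasting only later; the code for ongoing events makes that remainder visible.

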## CLINICAL INVESTIGATION SUMMARY IN LOCAL LANGUAGE

Hintergrund: Gangstörungen stellen ein relevantes Symptom bei Patient\*innen mit neurologischen Erkrankungen dar. Bei Multipler Sklerose (MS) können beispielsweise Symptome wie Schwäche und Spastik, Verlust der Propriozeption und Koordination, vestibuläre, kognitive und visuelle Dysfunktion, Fatigue und Schmerzen zu einer Gangbeeinträchtigung beitragen. Beim Idiopathischen Parkinsonsyndrom (PD) wird die Mobilität durch Rigor, Hypo- und Bradykinesie, Flexionshaltung und Haltungsinstabilität beeinträchtigt. Nach einem Schlaganfall ist eine hemiparetische, spastische Gehbehinderung ein häufiges Symptom bei ca. 75 % der Patient\*innen. Hereditäre Ataxien sind primär durch progrediente Koordinationsdefizite von Bewegung und Sprechen sowie einem breitbasigen, unkoordinierten, unsicheren Gang charakterisiert. Bei Patient\*innen mit spastischer Para- oder Tetraplegie, akuter oder chronischer entzündlicher demyelinisierender Polyneuropathie und Motoneuronerkrankung ist eine Gangstörung ebenso ein wesentlicher Faktor ihrer Behinderung, die zu Einschränkungen in ihrem Alltag führt. Zahlreiche Studien stellten fest, dass eine Gehbehinderung zu Depressionen und Angstzuständen beiträgt, die soziale Teilhabe und die Lebensqualität stark beeinträchtigt. Darüber hinaus wiesen einschlägige Studien auf den Zusammenhang zwischen Gehbehinderung und Erwerbstätigkeit bei Patient\*innen mit neurologischen Erkrankungen hin. Patient\*innen mit neurologischen Erkrankungen können aufgrund ihrer Gangstörung und Beeinträchtigung bei Aktivitäten des täglichen Lebens ihrer Arbeit nicht mehr nachgehen und sind bezüglich sozialer Aktivitäten beeinträchtigt. Neurologische Defizite wie Gang-, Gleichgewichts- und Koordinationsstörungen können durch intensives und repetitives aufgabenorientiertes Training reduziert werden. Motorisches Lernen, basierend auf dem Prozess der neuronalen Plastizität, kann bei Patient\*innen mit leichter bis schwerer Behinderung durch Neurorehabilitationsstrategien gefördert werden. Prinzipien einer effektiven Neurorehabilitation sind bereits bekannt und werden in der stationären und ambulanten Neurorehabilitation routinemäßig angewandt. In der stationären Rehabilitation dient etwa ein geräteunterstütztes Gangtraining (robot-assisted gait training, RAGT) dazu, um die Prinzipien des massierten (konzentrierten) Trainings, hoher Dosis, aufgaben- und zielorientierten Trainings unter progressiver Anpassung der Schwierigkeit und implizitem sowie explizitem Feedback zur Verbesserung des Ganges zu nützen.

Notwendigkeit für die Durchführung dieser Klinische Prüfung: Unseres Wissens untersuchte bisher keine Studie in der klinischen Routine eingesetztes RAGT bei verschiedenen Patient\*innengruppen mit neurologischen Erkrankungen in einem stationären Rehabilitationssetting. Der Zweck dieser Klinische Prüfung ist daher, in einer vergleichenden multiplen Fallstudie die Machbarkeit und Akzeptanz sowie die präliminären Effekte von RAGT bei Patient\*innen nach Schlaganfall, mit MS, PD, spastischer Para- oder Tetraplegie, hereditärer Ataxie, akuter / chronischer entzündlicher demyelinisierender Polyneuropathie und Motoneuronerkrankung zu untersuchen.

Methoden: Die vergleichende multiple Fallstudie wird am Reha Zentrum Münster, Tirol durchgeführt. 28 Patient\*innen nach schwerem Schlaganfall in der subakuten Phase (n=5) und nach mild bis moderatem Schlaganfall in der chronischen Phase (n=5), mit MS (n=5), PD (n=5), spastischer Para- oder Tetraplegie (n=2), hereditärer Ataxie (n=2), akuter / chronischer entzündlicher demyelinisierender Polyneuropathie (n=2) und Motoneuronerkrankung (n=2) im Alter von 18-99 Jahren werden anhand definierter Ein- und Ausschlusskriterien nach einem Screening für kognitive Beeinträchtigung und Gangstörung und schriftlicher informierter Einwilligung in diese klinische Prüfung eingeschlossen. Die Intervention ist in der klinischen Routine durchgeführtes RAGT: 45 min, 4x/Woche, 4 Wochen lang. Zur Baseline- und Postinterventionstestung werden Gang- und Gleichgewichtstests, Fragebögen und eine Zielevaluierung durchgeführt. Die Analyse beinhaltet eine deskriptive Statistik innerhalb der jeweiligen Krankheitsgruppen und eine Inferenzstatistik mit prä-post Analysen der Gesamtstichprobe.

